
### Methodological starting point of the Pro Kind project

#### Sample and sampling

The Pro Kind program was conducted from 2006 to 2012 in the three German states Bremen, Lower Saxony and Saxony (funded by the German Federal Ministry for Family Affairs, Senior Citizens, Woman and Youth BMFSJ [funding code: IIA6-25080820 V6], the Günter-Reimann-Dubbers Foundation [no funding code available], the Dürr Foundation [no funding code available], and the TUI Foundation [no funding code available]; the principal investigator of the intervention phase was TJ). The program was evaluated via longitudinal assessment [43] up to the children’s third birthday within the framework of a multicenter RCT. At the time of the baseline survey, *N* = 755 first-time mothers (TG *n* = 394, CG *n* = 391) participated, who were 12 to 28 weeks pregnant. In addition to first-time pregnancy the inclusion criteria were a financial risk factor (e.g., receiving welfare benefits or being in debt), as well as at least one further social or personal risk factor (e.g., being under age, lack of a school leaving certificate, having experienced abuse or neglect). In an a priori power analysis before the original RCT the sample size was estimated to be *N* = 775. We assumed (1) a minimum detectable effect sizes of ES = 0.20 (i.e., small effect), (2) a type I error rate (false positive) of α = .05, (3) statistical power (1 − *β*) of .80 (where *β* is the probability of making a Type II error, i.e., failing to detect a true effect if it is present) and (4) an attrition rate of 25% for this estimation.

The participants were recruited through various multipliers – especially through gynecologists, midwives, youth welfare offices, psychosocial counseling centers, and employment agencies [44]. After admission to the model project, those who at the time were between 12 and 28 weeks pregnant were randomly allocated to either the study group or the control group via a computer program (Efron’s biased coin design, strata: implementation location, being under age, and nationality of the mothers). Both groups had access to the regular support offered by the German welfare system and were informed about the latter. Furthermore, travel expenses to medical check-ups during as well as after pregnancy were covered as part of the panel maintenance. In addition, compensation was paid for the time participants invested for the program assessment.

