*Hypothesis 2.1*: The home visits result in improved parenting skills (less inappropriate parenting behavior)	Mother’s dysfunctional parenting	Parenting Scale (PS) ([66]), German version: target-group-specific adaptation by the authors	Primary outcome domain	Mother	Questionnaire
	Mother’s non-violent disciplining	Conflict Tactic Scale Child Report (CTS-CR [68]), interview of the children with picture cards. German version: translation by the AMIS group / Conflict Tactic Scale Parent Child (CTS-PC [67]), German version: target-group-specific adaptation by the authors		Child / Mother	Interview through trained test administrator (Child) / Questionnaire (Mother)]
*Hypothesis 2.2*: The home visits reduce or prevent child abuse and the frequency of physical violence	Mother’s child abuse	Conflict Tactic Scale Parent Child (CTS-PC) ([54]), German version: target-group-specific adaptation by the authors	Primary outcome domain	Mother	Questionnaire
	Mother’s “Minor” aggression	Conflict Tactic Scale Child Report (CTS-CR [68]), interview of the children with picture cards. German version: translation by the AMIS group / Conflict Tactic Scale Parent Child (CTS-PC) ([54]), German version: target-group-specific adaptation by the authors		Child / mother	Interview through trained test administrator (Child) / Questionnaire (Mother)
	Mother’s “Minor” physical violence				
*Hypothesis 2.3*: The home visits reduce or prevent child neglect	Mother’s physical neglect	Scale of the Multidimensional Neglectful Behavior Scale-Child Report (MNBS [53]), interview of the children with picture cards. German version: translation by the AMIS group.	Primary outcome domain	Mother	Questionnaire
	Mother’s emotional neglect			Child / mother	Interview through trained test administrator (Child) / Questionnaire (Mother)
	Mother’s cognitive neglect				
	Mother’s supervisory neglect				
*Hypothesis 3.1*: The home visits have a positive effect on the mother’s perceived social support	Mother’s Perceived social support	Questionnaire regarding social support (FSOZU-K6 [71])	Secondary outcome domain	Mother	Questionnaire
*Hypothesis 3.2*: The home visits influence the mother’s mental health	Mother’s mental stress	Depression-Anxiety-Stress Scale (DASS [70]), German version: target-group-specific adaptation by the authors	Primary outcome domain	Mother	Questionnaire

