### Data analysis

The primary and secondary analyses will be conducted on an intention-to-treat basis. Multilevel modeling will be used for statistical analyses of our primary and secondary outcomes. Prior to analysis, data will be checked for outliers, inconsistencies and possible transformation. We predict that our sample size will be large enough for our statistical tests to be robust regarding non-normally distributed variables. To reduce bias and loss of statistical power in our analysis of primary and secondary outcome indicators, we will use multiple imputations to estimate values for missing data. Power analyses (i.e., *sensitivity*) based on an attrition rate of 30% (*N* = 542 for the CATIs, CAPIs and developmental tests) given a type I error rate (false positive) of α = .05 and statistical power of 1− *β* = .80 resulted in a minimum detectable effect sizes of ES = 0.2. For an attrition rate of 40% (*N* = 465) a minimum detectable effect sizes of ES = 0.23 was estimated. To take that into account we analyze different outcome measures within one hypothesis, we will adjust our results for multiple hypothesis testing (MHT) to control the family-wise type I error rate.

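### The printed minimum detectable effects (0.2 at N = 542, 0.23 at N = 465) are too small for a two-sided .05 test with 80% power, and they precede the promised multiplicity adjustment

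*Protocol article*

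**What the plan says.** The Data analysis section of the protocol article reports a sensitivity power analysis for the follow-up, "given a type I error rate (false positive) of α = .05" and "statistical power of 1− *β* = .80". For 30% attrition (N = 542) this "resulted in a minimum detectable effect sizes of ES = 0.2"; for 40% attrition (N = 465), "a minimum detectable effect sizes of ES = 0.23 was estimated". It does not say whether the test is one-sided or two-sided, and it mentions no gain from covariates. The next sentence commits to family-wise type I error control where several outcome measures serve one hypothesis.

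Sample and sampling gives the calculation for the original randomised trial: N = 775 from ES 0.20, alpha .05, power .80 and "an attrition rate of 25% for this estimation". Sidedness is not stated there either.

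Two other places bear on sidedness. Hypothesis 3.2, a primary outcome domain in Table 1, has no direction: "The home visits influence the mother’s mental health". And the section on current research results reports a Wald statistic of 4.05 on 1 df with p = .044.

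**The concern.** An alpha of .05 with no qualifier is normally read as two-sided. On that reading both MDEs are too small for the stated power. Rounding does not explain the pair: 0.241 could be printed as 0.2, but 0.23 at the smaller sample lies below the two-sided value at the larger one.

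The MDEs also sit beside a promise of multiplicity adjustment that they do not reflect. The article says the results are meant to inform future prevention programmes and help legitimise early childhood investment. A reader who takes the printed figures at face value would credit the follow-up with 80% power for effects of 0.20 to 0.23 SD. Under two-sided testing without covariate gain it does not have that.

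**Working it through.** **Inputs.** Alpha .05, power .80, N = 542 and 465 (Data analysis). ES 0.20, alpha .05, power .80, 25% attrition, N = 775 (Sample and sampling). Assumed here: equal arms, SD = 1, comparison of two means.

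**Formula.** MDE = (z_alpha + z_power) × √(4/N), with z_power = 0.8416. z_alpha is 1.9600 two-sided and 1.6449 one-sided. √(4/542) = 0.0859 and √(4/465) = 0.0927. The noncentral t changes results only in the fourth decimal.

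| N | printed | one-sided (normal; t) | two-sided (normal; t) |
|---|---|---|---|
| 542 | 0.2 | 0.2136; 0.2139 | 0.2407; 0.2411 |
| 465 | 0.23 | 0.2306; 0.2310 | 0.2598; 0.2604 |

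**Reproducing the plan.** One-sided, 0.23 is matched, and 0.2 is matched only to one decimal.

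**Power for the printed effects**, as Φ(d/√(4/N) − z_alpha):
- N = 542, d = 0.20: 0.20/0.0859 = 2.328. Two-sided Φ(0.368) = 64%; one-sided Φ(0.683) = 75%.
- N = 465, d = 0.23: 0.23/0.0927 = 2.480. Two-sided Φ(0.520) = 70%; one-sided Φ(0.835) = 80%.

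**A second route to the printed figures.** Covariates explaining R² of the variance multiply the MDE by √(1 − R²). With R² = 0.22, 0.2411 × 0.883 = 0.213 and 0.2604 × 0.883 = 0.230. At the printed rounding, any R² from about 0.19 to 0.25 fits both.

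**Sidedness of the trial's reported tests.** √4.05 = 2.012, whose two-sided p is .044, as printed. That test was two-sided.

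**The original N = 775.** n per arm = 2(z_alpha + z_power)²/0.20².
- One-sided: 2 × 2.4865²/0.04 = 309.1, so 310 per arm and 620 in total. 620 × 1.25 = 775, the stated figure. To retain 620 after 25% loss, 620/0.75 = 827 are needed.
- Two-sided: 2 × 2.8016²/0.04 = 392.4, so 393 per arm (394 with the t distribution), 786 to 788 in total. Dividing by 0.75 gives 1,048 to 1,051.
- 775 × 0.75 = 581. Then 0.20/√(4/581.25) = 2.411, so power is Φ(0.766) = 78% one-sided and Φ(0.451) = 67% two-sided.

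**Multiplicity (illustration).** The article names neither a method nor a number of tests. Taking Bonferroni over m measures as an assumption, the two-sided MDEs are:

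| m | N = 542 | N = 465 |
|---|---|---|
| 1 | 0.24 | 0.26 |
| 2 | 0.27 | 0.29 |
| 4 | 0.29 | 0.31 |
| 8 | 0.31 | 0.33 |

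A one-sided test with m = 2 has the same critical value as an unadjusted two-sided test, so it already gives 0.241 and 0.260.

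**The case against.** The best counter-argument is that the figures need not be wrong. A reader might infer that they can only have come from a hidden one-sided test. The documents do not support that for the MDEs. If one-sided 0.214 may pass as 0.2, a two-sided analysis with R² near 0.22 must be allowed the same rounding, and it fits both figures. The planned multilevel models make a covariate-adjusted MDE conceivable. The one-sided reading rests mainly on 620 × 1.25 = 775, which belongs to the original trial's calculation.

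Most hypotheses are also directional, so one-sided tests could be declared and justified, and sidedness may be set out in a plan not shown. Both points are fair. They do not settle the matter, because the article prints numbers that do not follow from its printed inputs on the ordinary reading, and whichever assumption closes the gap has to be stated with them. One-sided testing also sits badly with the non-directional primary hypothesis 3.2 and with the two-sided test already reported.

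The multiplicity figures depend on assumed inputs. Measures within a hypothesis are likely to be correlated, and step-down or resampling methods cost less than Bonferroni. A reader might also infer that every primary hypothesis has an MDE of 0.27 to 0.33. That does not follow: hypotheses tested on one overall score, such as 1.4 (ILK) or 3.6 (FLZ), need no adjustment.

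Finally, the cohort is already randomised and its size is fixed, and a null result will be judged by its confidence interval rather than by a planning MDE. This limits the consequence to the stated sensitivity; it does not make the printed figures right.

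**Conclusion.** The point holds as a mismatch between printed figures and printed inputs. Two-sided at .05 with 80% power, the follow-up can detect 0.24 at N = 542 and 0.26 at N = 465, not 0.2 and 0.23. This assumes equal arms, a comparison of two means and no covariate gain. Either one-sided testing or an R² of about 0.22 would account for the printed values; neither is declared, and the documents do not show which was used. It would therefore go too far to say outright that the follow-up lacks its claimed power. The shortfall is conditional on two-sided testing without covariate gain, or on the promised adjustment where a hypothesis has several measures.

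The multiplicity gap exists under either sidedness, because the MDEs use the full .05. The original N = 775 falls short of .80 after its own planned attrition on both readings (78% and 67%), again without covariate gain.

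**What to change.** In Data analysis:
- State the sidedness of the tests. Two-sided fits hypothesis 3.2 and the trial's earlier reported tests.
- State any covariate R² behind the MDEs.
- Print the unadjusted two-sided MDEs as 0.24 (N = 542) and 0.26 (N = 465).
- For primary hypotheses with several measures, add the MDE at the adjusted alpha, and state the method and the number of measures as assumptions. With Bonferroni over 2 to 8 measures this would read 0.27 to 0.31 at N = 542 and 0.29 to 0.33 at N = 465. Hypotheses tested on one score stay at 0.24 and 0.26.

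In Sample and sampling, note that attrition was applied as × 1.25 rather than ÷ 0.75, and that 775 did not secure 80% power for 0.20 after 25% loss.

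The cost is a few sentences and a small recalculated table. No additional families are needed, and the only drawback is a less favourable stated sensitivity.

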#### Subgroup analysis

We will conduct preplanned analyses for different participants’ and child characteristics contributing to positive effects in the original trial (see [43, 45–47]). For this purpose, we consider the influence of different factors (i.e., maternal age at pre-assessment and number of mother-related risk factors at pre-assessment and child gender). Additionally, we will analyze subsequent births as a mediating factor of treatment efficacy in a preplanned subgroup analysis as a greater number of second births in the treatment group was a main effect in the original trial. Due to earlier findings [45], all primary and secondary outcomes will be analyzed with regard to any differential effects, while controlling for children’s gender.

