### Current research results from the home-visiting program Pro Kind

Data collection at the time points at 6, 12 and 24 months after birth of the reference child showed small positive effects of the Pro Kind program on maternal feelings of parental self-efficacy (*β* = .03; Wald = 4.05; *df* = 1; *p* = .044), social support (*β* = .04; Wald = 3.85; *df* = 1; *p* = .050) and their knowledge about child-rearing (*β* = .03; Wald = 3.43; *df* = 1; *p* = .064) [43]. In addition, fewer women in the treatment group stated that they suffered from depressive mood 24 months after birth (OR 0.54, *p* = .070]. This finding was confirmed by administrative health insurance data that showed that fewer mothers in the treatment group used antidepressants (*p* = .040^1^). The increased maternal wellbeing may be one reason why in the treatment group fewer pregnancy terminations (conditional on a further pregnancy) than in the control group were observed (OR 0.54, *p* = .090). This might also as a consequence have led to a higher rate of second births 36 months after birth (OR, 1.48, *p* = .030). Regarding the children, the intervention resulted in an improvement in the cognitive development of the girls in the treatment group (at 6 months, ES 0.29, *p* < 0.05; at 12 months, ES 0.28, *p* < .05; at 24 months, ES 0.24, *p* < .01), whereas no improvement could be found in the boys’ cognitive skills. One possible explanation for the gender-specific effect could be that the intended treatment, consisting of the parents reading to, and singing with, their children, was implemented more often with female children compared to male children [45–47].

In addition, the model project Pro Kind is being evaluated by encompassing economic research, for which the most important goal was, and is, to conduct a cost-benefit analysis. The costs for providing the home-visiting program were thereby contrasted with the monetized benefits of the intervention, whereby, in conclusion, the program’s return on investment (ROI) can be determined. The cost of an average intervention was approximately €8.700 [48]. Since the home-visiting program Pro Kind seeks to achieve improvements in several different domains, the saving effects should be different in the various domains and concern different fiscal areas.

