Hypothesis 4.4: The home visits influence the timing or frequency of a renewed pregnancy and births	Renewed pregnancy	Questionnaire about intended and realized fertility (Siedler et al., 2009). Integrated Employment History provided by the Institute of Employment Research (IAB)	Secondary outcome domain	Mother/ Institute of Employment Research (IAB)	Questionnaire/ administrative data
	Renewed desire to have children				
	Abortions Births				
Hypothesis 5.1: The home visits improve the mothers’ physical health	Mother’s physical health	12-Item Short Form Survey (SF-12 [79])	Secondary outcome domain	Mother	Questionnaire
Hypothesis 5.2: The home visits increase the frequency of pediatric primary care use (e.g., screenings, vaccinations, child’s oral health care and dentist visits)	Frequency of pediatric primary care use	KiGGS questionnaire [80] physician visits with ICD Z	Secondary outcome domain	Mother health insurance companies	Questionnaire/administrative data
Hypothesis 5.3: Home visits reduce the children’s hospital visits (outpatient or inpatient) caused by accidents and injuries	Number of child’s injuries	Hospital admission and physician visits with ICD S and T	Secondary outcome domain	Health insurance companies	Administrative data

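### Subsequent births, a post-randomisation variable that treatment reportedly increased, should be taken out of the subgroup analysis and studied in a separate exploratory mediation model

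*Protocol article*

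**What the plan says.** The Subgroup analysis section first lists the factors "maternal age at pre-assessment and number of mother-related risk factors at pre-assessment and child gender". It then adds that "we will analyze subsequent births as a mediating factor of treatment efficacy in a preplanned subgroup analysis", and gives the reason: "as a greater number of second births in the treatment group was a main effect in the original trial".

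Three other places bear on this.

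- **Timing.** Under Sample and sampling, "those who at the time were between 12 and 28 weeks pregnant were randomly allocated to either the study group or the control group".
- **Treatment effect on births.** The section on current research results reports a "higher rate of second births 36 months after birth (OR, 1.48", with p = .030).
- **Births as an outcome.** Hypothesis 4.4 reads "The home visits influence the timing or frequency of a renewed pregnancy and births", and Table 1 places it in the secondary outcome domain.

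The Data analysis section adds: "The primary and secondary analyses will be conducted on an intention-to-treat basis".

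**The concern.** A valid subgroup factor is fixed before treatment can act on it, so that randomisation still balances the arms within each level. The pre-assessment factors meet that condition, and so does child gender, because the child was already conceived at randomisation. A subsequent birth does not meet it. The article picks births because treatment changed their number, and that same fact makes them unsuitable for defining subgroups.

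Two things follow if the sentence is carried out as a comparison of arms within birth strata.

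1. **Selection.** If the programme led some women to have a further child, the women with a second birth are differently selected in the two arms, and so are the women without one. Anything that drives both further births and later outcomes then enters the within-stratum contrast.
2. **Target.** A within-stratum contrast describes a treatment difference given birth status. It is not an indirect effect, which is what a mediation question asks for.

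At stake is the reading of one additional analysis. A difference between women with and without a second child could be reported as preplanned evidence about mechanism when part of it reflects selection.

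**Working it through.** **Inputs from the article.** OR 1.48 and p = .030 for second births at 36 months; arms of 394 and 391; a detectable effect of 0.2 SD at N = 542. The arm sizes sum to 785 while the article prints N = 755, so several sample sizes are tried below. The second-birth rates are not given and have to be assumed.

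**Step 1: what birth rates fit the reported odds ratio?** The counts are not printed, so the OR cannot be recomputed, but its coherence can be checked.

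SE(ln OR) = ln(1.48) / z(0.985) = 0.392 / 2.170 = 0.181, which gives a 95% CI of about 1.04 to 2.11.

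Setting √[1/(n₁p₁(1−p₁)) + 1/(n₀p₀(1−p₀))] = 0.181, with p₁ tied to p₀ by the OR, gives:

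| n treated / control | control rate | treated rate |
|---|---|---|
| 394 / 391 | 16.8% | 23.0% |
| 394 / 361 | 17.9% | 24.4% |
| 290 / 290 | 26.9% | 35.3% |
| 250 / 250 | 40.2% | 49.9% |

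These rates are inferred. They make 20% to 40% a reasonable range to assume for the control arm.

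**Step 2: bias within strata when nothing is true.** This was simulated with 4,000,000 records. Treatment is randomised 1:1 and births have a marginal OR of 1.48. Neither treatment nor births affects the outcome. An unmeasured factor U has a log-OR of 0, 0.5 or 1.0 per SD on births and a correlation of 0.3 or 0.5 with the outcome (all assumed). Differences, treated minus control in SD, at a 30% control rate:

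| log-OR of U on births | correlation of U with outcome | births stratum | no-births stratum |
|---|---|---|---|
| 0 | 0.3 | −0.003 | 0.000 |
| 0 | 0.5 | −0.003 | 0.000 |
| 0.5 | 0.3 | −0.015 | −0.013 |
| 0.5 | 0.5 | −0.021 | −0.023 |
| 1.0 | 0.3 | −0.026 | −0.021 |
| 1.0 | 0.5 | −0.042 | −0.036 |

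Over control rates of 20%, 30% and 40% with U present, the differences run from −0.011 to −0.045. A variant with control rates of 20% or 30% and a stronger U (log-OR 1 to 1.5) gives −0.017 to −0.053. Overall differences lie between −0.003 and 0.000, which shows the simulation noise. The sign is negative only because U was assumed to raise both births and outcome; opposite directions would reverse it.

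Relative to 0.2 SD, the largest value is 0.053 / 0.2, about a quarter, and the smallest is 0.011 / 0.2, about one twentieth.

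**Step 3: what the strata show under pure mediation.** Assume 30% births in control, no confounding, and a birth that shifts the outcome by 1 SD with no other treatment effect. The control odds are 0.30/0.70 = 0.4286; multiplied by 1.48 they are 0.634, so the treated rate is 38.8%. The true indirect effect is (0.388 − 0.300) × 1 = 0.088 SD, and the total effect is the same. The simulated strata give 0.000 and −0.001. Those values are the correct direct effect, which is zero here. The indirect effect appears only when the overall effect is set against them: 0.088 − 0 = 0.088.

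**The case against.** The strongest reply is that the sentence names mediation as its aim, and that a treatment effect on births is the usual reason for a mediation analysis. It never says outright that the arms will be compared within birth strata. It is set apart from the list of baseline factors, and the label may be loose wording for a proper mediation model. An article may leave the model, the effect definitions and the confounder set to a fuller plan. Most of this stands. The stratified comparison is the natural reading of the words but not the only one, and the absence of model detail is not the fault. What remains is that the text names a subgroup analysis as the vehicle for a mediation question.

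Four stronger conclusions might be inferred, and the documents do not support them.

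- **That stratifying can never inform mediation.** Step 3 shows otherwise: without confounding, the strata return the direct effect, and comparison with the overall effect recovers the mediated part.
- **That the bias is about 0.11 SD.** This figure comes from assuming 30% control births, treating (0.388 − 0.300) / 0.388 = 22.7% of treated women with a second birth as induced, and giving them a 0.5 SD difference: 0.227 × 0.5 = 0.11. It also assumes that treatment only adds births, and it applies to one stratum. On the same inputs the other stratum gives (0.088 / 0.70) × 0.5 = 0.06. None of these inputs is in the article except the OR.
- **That the plan contradicts its intention-to-treat commitment.** That commitment covers the primary and secondary analyses, and this analysis is an addition to them.
- **That a formal mediation model removes the problem.** It also needs the absence of unmeasured confounding between births and outcome.

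**Conclusion.** The point holds in limited form and should be fixed. Births follow randomisation, were reportedly increased by treatment and are themselves an outcome, so they do not belong among subgroup factors. If the sentence is followed as a comparison within birth strata, the contrasts lose the protection of randomisation and do not on their own report an indirect effect.

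The size is probably modest: about 0.01 to 0.05 SD under a true null, given assumed control birth rates of 20% to 40% and an assumed common cause of births and outcome, and near zero without one. The primary and secondary intention-to-treat comparisons, the sample size and the power figures are untouched.

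**What to change.** Remove subsequent births from the subgroup analysis. Limit subgroup (interaction) analyses to maternal age and number of risk factors at pre-assessment, and child gender. Keep births as the Hypothesis 4.4 outcome, which is already planned. Replace the sentence with something like:

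> In a separate, exploratory mediation analysis we will estimate direct and indirect effects of the programme through subsequent births that precede the outcome assessment, adjusting for baseline confounders of the relation between births and outcome, with a sensitivity analysis for unmeasured confounding.

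The cost is one sentence and one extra exploratory model, with no change to the sample size. The drawback is that the model still rests on an assumption of no unmeasured confounding that the data cannot test. That is why it should be labelled exploratory and carry the sensitivity analysis.
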